### Statistical analysis

We will report according to CONSORT standards.

Regression models will be used to estimate the treatment effects (with 95% confidence intervals) and will be adjusted for important covariates (prior fracture history and age). The final statistical analysis will include data from patients from the control arm and intervention arm(s) continuing beyond the interim analysis from both the first and second stages of the trial. The analysis needs to allow for the adaptation made at the interim analysis in order to ensure that the probability of a type I error (false positive result) is controlled. It is proposed to use the analysis method described by Bretz and colleagues [44], applying a Dunnett correction to the comparisons between the intervention arms and the control arm at the first stage and at the second stage unless an intervention arm is dropped.

Complier-average causal effect will be estimated to assess the impact of adherence on the effect of the interventions.

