**Methods/Design:**

Six hundred people with osteoporosis and a clinically diagnosed vertebral fracture will be recruited and randomly allocated to one of three management strategies, usual care (control - A), an exercise-based physiotherapy intervention (B) or a manual therapy-based physiotherapy intervention (C). Those in the usual care arm will receive a single session of education and advice, those in the active treatment arms (B + C) will be offered seven individual physiotherapy sessions over 12 weeks. The trial is designed as a prospective, adaptive single-blinded randomised controlled trial. An interim analysis will be completed and if one intervention is clearly superior the trial will be adapted at this point to continue with just one intervention and the control. The primary outcomes are quality of life measured by the disease specific QUALLEFO 41 and the Timed Loaded Standing test measured at 1 year.

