### Baseline assessment

After participants have been assessed for eligibility and consent has been gained, baseline assessment will be carried out. Questionnaires and physical assessment will be completed (both participant and assessor will be unaware of allocation at this appointment). The baseline measures are summarised in Table 1.

**Table 1 T1:** Summary of outcomes and assessment schedule

**Tests**	**Administered by**	**Week 0**	**Month 4**	**Month 6**	**Month 9**	**Month 12**
Functional Co-morbidities Index	Self	*√*				
QUALEFFO 41	Self	*√*	*√*	By post	By post	*√*
EQ-5D-5 L	Self	*√*	*√*	By post	By post	*√*
Physical Activity Scale for the Elderly	Self	*√*	*√*	By post	By post	*√*
Timed Load Standing	Assessing therapist	*√*	*√*			*√*
Flexicurve ruler	Assessing therapist	*√*	*√*			*√*
The Short Performance Physical Battery	Assessing therapist	*√*	*√*			*√*
The Functional Reach test	Assessing therapist	*√*	*√*			*√*
6 minute walk test	Assessing therapist	*√*	*√*			*√*
10 point visual analogue scale	Self	*√*	*√*			*√*

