### Data and statistical analysis

#### Interim analysis decision rules

The decision to adapt the trial following the interim analysis and whether to drop one of the treatment arms, or to continue, will be made by the Trial Steering Committee based upon the recommendations of the independent data monitoring committee (IDMC). The IDMC will base their decision on the data from the interim analysis, using the rules below, together with data on adverse events, falls and further fracture history. An interim analysis will be conducted when the 16-week follow-up data are available for 75 patients per treatment arm. The aim of this interim analysis is to terminate either the manual therapy or exercise therapy arm if it appears to be poorly performing relative to the other intervention or to the control, or to terminate the trial completely if both intervention arms appear to be performing poorly relative to the control.

Although the integrity of the trial in terms of type I error control does not require pre-specification of the decision rule to be used at the interim analysis, as a guideline for the IDMC the interim analysis decision rule will be based on comparison of the estimated mean change from baseline in the QUALEFFO score for each of the three study arms as follows:

a) If the mean change from baseline of the QUALEFFO score for an intervention arm is not more than 0.5 points greater than that for the control arm, that intervention arm will be dropped from the study. Note that under this rule both intervention arms might be dropped, in which case the study would stop due to futility.

b) If the mean change from baseline of the QUALEFFO score for one intervention group is more than 2 points higher than for the other group, the intervention with the lower mean change from baseline will be dropped from the study.

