#### Sample size

The initial sample size calculation is based on a traditional approach to a three-arm trial. We wish to detect a standardised effect of 0.4 in the QUALEFFO; at 80% power and an alpha of 0.05 we would require 180 to 200 participants in each arm or 540 to 600 people (we will use 600 people as the upper limit).

A simulation study was conducted to estimate the power of the study assuming the interim decision rules above were used. The sample size for the interim analysis was chosen to be 75 per arm. This ensures that the power is high while the probability of continuing with an ineffective treatment is sufficiently low. If the true (unknown) treatment effect for an intervention is equal to the control, the probability of dropping that intervention at the interim analysis is approximately 73%. If neither intervention is truly superior to the control, the probability of stopping the entire study at the interim analysis is approximately 60%. Based on this interim analysis sample size the standard error of the estimated difference between the intervention arms and the control arm at the interim analysis will be 0.82.

In the adaptive design of the type proposed, the power of the study may be defined as the probability, given a truly effective intervention, that the intervention remains in the trial at the interim analysis and leads to a significant result in comparison to the control in the final analysis. The specified sample size gives 94% power if the better of the two intervention arms has a true standardised treatment effect of 0.4.

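### The final model's named covariates leave out the baseline value of each primary outcome, which gives up precision and leaves chance baseline imbalance in the estimate

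*Protocol article*

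**What the plan says.** The Statistical analysis section states "Regression models will be used to estimate the treatment effects (with 95% confidence intervals" and that these models "will be adjusted for important covariates (prior fracture history and age". No other covariate is named there or elsewhere in the article. The section does not say whether the dependent variable is the 12-month value or the change from baseline.

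The two primary outcomes are QUALEFFO 41 and, in the words of the abstract, "the Timed Loaded Standing test measured at 1 year". Under Baseline assessment, "The baseline measures are summarised in Table 1", and that table shows both outcomes recorded at week 0 and again at months 4 and 12. According to the Recruitment section, the baseline assessment comes before the call to the randomisation centre.

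Change from baseline appears only under Interim analysis decision rules, where the guideline for the IDMC rests on "comparison of the estimated mean change from baseline in the QUALEFFO score for each of the three study arms".

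**The concern.** The baseline score is likely to be the strongest single predictor of the same score a year later. It is collected on everyone before allocation, so it can be used without risk to validity. The article names two covariates and leaves this one out.

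Two things follow, whichever outcome metric is intended. The confidence intervals are wider than the data require. And if the arms differ at baseline by chance, part of that difference passes into the treatment estimate: in one direction if the 12-month value is analysed, in the other if change is analysed. Because the section makes estimates with 95% intervals the reported result, interval width matters even when power is ample.

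**Working it through.** **The plan's own figures.** Inputs from the Sample size and Interim analysis decision rules sections: 75 per arm at the interim, SE of the interim difference 0.82, thresholds of 0.5 and 2 points, a standardised effect of 0.4, and 600 participants.

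- Implied SD: 0.82 / √(2/75) = 5.02 points, so 0.4 SD = 2.01 points.
- Chance of dropping an arm with no effect: Φ(0.5/0.82) = 72.9% (stated: about 73%).
- Chance of stopping when neither arm works, from a bivariate normal with correlation 0.5: 59.3% (stated: about 60%).
- Power was simulated with 200,000 runs per scenario, applying rules (a) and (b), an inverse-normal combination of stages and a closed test with Dunnett correction at one-sided 0.025. It came to 93–96% across assumed effects in the second arm (0, 0.2, 0.4 SD), assumed 4-to-12-month correlations (0.5 to 1), and with or without reallocating a dropped arm's places (stated: 94%).

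The stated power therefore does not depend on baseline adjustment.

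**Precision.** Let r be the baseline-to-12-month correlation. The article does not give it, so 0.5 to 0.7 is assumed, with equal variance at both times. The variance with baseline adjustment is 1 − r² relative to the 12-month value alone. Relative to the change score it is (1 − r²) / (2(1 − r)) = (1 + r)/2. The interval narrows by 1 minus the square root of each ratio.

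| r (assumed) | Variance ratio vs 12-month value | CI narrower by | Variance ratio vs change | CI narrower by |
|---|---|---|---|---|
| 0.5 | 0.75 | 13% | 0.75 | 13% |
| 0.6 | 0.64 | 20% | 0.80 | 11% |
| 0.7 | 0.51 | 29% | 0.85 | 8% |

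These ratios compare with a model that has no covariates. The planned model already holds age and fracture history, so the relevant r is the partial correlation given those two. If it is lower than the raw one, the gain over the 12-month value is somewhat smaller. Under the change reading, a lower r makes (1 + r)/2 smaller, so that gain is not reduced by this argument.

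**Chance imbalance.** With 600/3 = 200 per arm, the SE of a baseline difference is √(2/200) = 0.10 SD, with a 95% range of ±0.196 SD. A difference at that edge shifts the estimate as follows:

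- 12-month value: r × 0.196 = 0.098 SD (r = 0.5) to 0.137 SD (r = 0.7).
- Change: −(1 − r) × 0.196 = −0.098 SD to −0.059 SD.

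Against the 0.4 SD target this is 0.059/0.4 = 15% to 0.137/0.4 = 34%.

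**Power after the change.** The simulation was rerun with the reduced final-stage variance (r = 0.5 and 0.7, both comparators), leaving the interim rule as it is. Power was 95.7–96.7%, against 94.7–95.8% in the matching runs without baseline. The ceiling comes from the interim, where a truly effective arm is lost in about 3–4% of runs.

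**Interim rule, if baseline-adjusted.** Taking 0.82 as the SE of an unadjusted change comparison and multiplying it by √0.75, √0.80 and √0.85 gives 0.71, 0.73 and 0.76.

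- Rule (a) drops an ineffective arm: 73% becomes about 75–76%.
- Rule (a) drops an arm with a true 0.4 SD effect: Φ((0.5 − 2.01)/0.82) = 3.3% becomes 1.7–2.3%.

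**The case against.** The strongest reply is that this is one sentence in a condensed article. It fixes neither the dependent variable nor the model form, and the full protocol or analysis plan may well add the baseline value. That lowers confidence about what will finally be done. It does not remove the point: the sentence names its covariates rather than leaving them open, and if a fuller document adds baseline, the published list should agree with it.

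The other side is also right that several stronger inferences do not hold.

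- *The estimate is biased.* It is not. Randomisation keeps it unbiased on average; the shifts above are conditional on the baseline difference that happens to occur.
- *The trial wastes a large share of its sample.* Converting the ratios 0.75 to 0.51 gives 33% to 96% more participants, but that assumes a covariate-free analysis of the 12-month value, which the article never states. Under the change reading the equivalent is 33% down to 18% (1/0.75 and 1/0.85). In either case the stated power is already 94%.
- *The interim and final analyses aim at different quantities because one uses change.* Under randomisation, the change-score, follow-up-score and baseline-adjusted differences at a given time have the same expectation. They differ in variance.
- *The interim thresholds are lost in noise.* The 0.5-point threshold is 0.5/0.82 = 0.6 SE, but the 2-point threshold is 2/0.82 = 2.4 times 0.82. The rule is also only a guideline, read together with adverse events, falls and fractures, and its wording does not rule out model-adjusted means.

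**Conclusion.** The point holds as an avoidable loss of precision. The named covariate list omits the baseline QUALEFFO 41 and TLS values although both are collected before randomisation. For an assumed correlation of 0.5 to 0.7, the 95% interval could be about 13–29% narrower if the 12-month value is analysed (somewhat less if age and fracture history already explain part of the outcome), or about 13% down to 8% narrower if change is analysed. A chance imbalance at the edge of its 95% range would move the unadjusted estimate by 0.06 to 0.14 SD.

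The planned analysis is valid without the change and its stated power reproduces. Power would rise by at most about three points, and the effect on the interim rule is small. All the sizes rest on the assumed correlation and on equal variances at the two times. The article supports no claim of bias or of inadequate power on this ground.

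**What to change.** In the Statistical analysis section, replace the covariate wording with: *Treatment effects at 12 months will be estimated by regression adjusted for the baseline value of the outcome, prior fracture history and age.* Apply this to each primary outcome, and state that these baseline-adjusted estimates supply the stage-wise test statistics in the combination test. This needs only a change of wording: the data are already collected, and with recruitment still under way the covariates can be fixed before unblinded results are seen.

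Optionally, use the baseline-adjusted 4-month difference in interim rules (a) and (b). This has a small cost. With unchanged thresholds the operating characteristics move, so the SE of 0.82 and the 73%, 60% and 94% figures in the Sample size section would have to be recomputed and restated.

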### Secondary outcomes

There are a number of outcomes included seeking to assess a number of different aspects of symptoms, function and activity. We will be piloting the package, and if the burden of measurement is too great, some measures will be dropped and the protocol amended.

The Functional Co-morbidities Index will be completed as other diseases are likely to be present in this older population which might affect physical outcomes [33].

Spinal curvature and flexed posture will be described by recording height (cm) and thoracic kyphosis. Thoracic kyphosis will be measured using a flexicurve ruler with the patient in a standing position to calculate an index and angle of kyphosis [34].

Other outcomes include measures of balance, mobility and physical activity. Each test is reliable and valid, has been used with older, community dwelling adults and shown to be responsive in previous rehabilitation studies.

•The Short Performance Physical Battery will be used to assess lower extremity physical function [35]. Poor performance is predictive of future disability, hospitalisation and care needs.

•The Functional Reach Test will be used to specifically evaluate standing balance and to act as a predictor of falls risk [36].

•A 6 minute walk at self-selected speed over a 30 metre course will be used to measure exercise endurance; an important parameter of functional, community mobility [37].

•The Physical Activity Scale for the Elderly is a short, self-administered questionnaire to assess activity in the past week [38].

•The EuroQol EQ-5D-5 L is a short, generic measure of QoL and will be completed to facilitate the assessment of cost-effectiveness and also to give a comparison with other clinical conditions [39].

•Participants will be asked to specifically rate back pain on activity and at rest using a 10 point visual analogue scale.

•Information about fractures and falls will be collected using a standardised definition and a prospective participant completed event calendar. These will be mailed to participants monthly during the year of the study and participants will be telephoned by the trial co-ordinator to promote adherence and to check this information is captured precisely [40].

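### The Functional Co-morbidities Index, collected once at baseline for its possible effect on physical outcomes, is listed under secondary outcomes and left out of the named model covariates, so a modest possible gain in precision goes unused

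*Protocol article*

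**What the plan says.** Three places in the protocol article bear on this.

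- **Secondary outcomes** gives the only stated reason for the measure: "The Functional Co-morbidities Index will be completed as other diseases are likely to be present in this older population which might affect physical outcomes".
- **Baseline assessment, Table 1** has the index self-completed and ticked at week 0 only. Every other row of the table is repeated at month 4 or later. Under Procedures, randomisation follows the baseline assessment.
- **Statistical analysis** says the regression models for the treatment effects "will be adjusted for important covariates (prior fracture history and age". These two covariates are the only ones named.

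No other section gives the index a role in the analysis. Outcome measures presents Timed Loaded Standing as the primary measure of physical function. The Short Performance Physical Battery, Functional Reach Test and 6 minute walk are physical tests among the secondary outcomes.

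**The concern.** A variable measured once, before allocation, cannot be an outcome of treatment, so its place under Secondary outcomes is a misclassification. The reason given for collecting it is the reason one gives for a prognostic covariate, yet the covariate list omits it. The stated rationale concerns physical outcomes and therefore reaches a primary endpoint.

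What is at stake is efficiency. If comorbidity does predict the physical outcomes over and above the covariates already in the model, adjusting for it would narrow the confidence intervals using data that are collected anyway. There is also a small practical risk. The Secondary outcomes section allows measures to be dropped if the burden proves too great, and a covariate filed there could be dropped as though it were an outcome.

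**Working it through.** **The plan's own power figure.** Sample size gives 75 per arm at the interim, an interim standard error of 0.82, a target of 0.4 SD ("We wish to detect a standardised effect of 0.4 in the QUALEFFO"), a maximum of 600 (so 200 per arm with equal allocation), and 94% power.

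- Implied SD = 0.82 / sqrt(2/75) = 5.02 QUALEFFO points.
- Probability of dropping a null arm = Φ(0.5/0.82) = 72.9%, against a stated 73%.
- Probability of stopping when both arms are null = 59.3% from the bivariate normal (59.5% by simulation), against a stated 60%.
- Power was simulated with the interim rules, inverse-normal combination and Dunnett closed testing at one-sided 0.025. With 200 per arm and a null or half-effective second arm it is 94.0% to 94.2%. In the other variants (second arm equally effective, or a dropped arm's participants reallocated) it is 94.6% to 95.8%.

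The 94% is therefore reproduced with no covariate term for comorbidity.

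**What adjustment could add.** Let r be the partial correlation of the index with the outcome, given the covariates already in the model. The documents do not state it, so 0.1 to 0.3 is an assumed range.

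- Standard error ratio = sqrt(1 − r²). This does not depend on the sample size.
- Equivalent extra participants per arm = 200/(1 − r²) − 200.
- SD of the shift in the unadjusted difference due to chance imbalance = r × sqrt(2/200) = 0.10 r, in outcome SDs.

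| Assumed r | SE ratio | SE cut | Extra per arm of 200 | Imbalance shift (SD) | Adaptive power at 0.4 SD |
|---|---|---|---|---|---|
| 0 | 1.000 | 0 | 0 | 0 | 95.9% |
| 0.1 | 0.995 | 0.5% | 2.0 | 0.01 | 95.9% |
| 0.2 | 0.980 | 2.0% | 8.3 | 0.02 | 96.2% |
| 0.3 | 0.954 | 4.6% | 19.8 | 0.03 | 96.8% |

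The power column takes a null second arm with a dropped arm's participants reallocated, which is why it starts at 95.9%. It is only illustrative, because the 0.4 SD target is set for QUALEFFO. For Timed Loaded Standing the article gives a 2.6 second difference but no SD, so the shifts cannot be turned into seconds.

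**Imbalance and precision are the same quantity.** At 200 per arm the unadjusted variance is 2/200 = 0.0100 in squared outcome SDs. At r = 0.3 the part due to chance imbalance is 0.03² = 0.0009, which is 9% of 0.0100 and equals r². Removing the imbalance is the precision gain and should not be counted as a second harm.

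**Cost of the extra term.** With 400 participants in a two-arm comparison, estimating one more coefficient costs roughly 1/400 = 0.25% of the variance. The gain is 1% of the variance at r = 0.1 and 9% at r = 0.3.

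**The case against.** The strongest reply has four parts.

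1. **The article is condensed.** A fuller covariate list may exist in an analysis plan that is not shown. Adjusting for two prespecified baseline covariates is also valid, and nowhere does the article promise to adjust for the index. This stands in part: the sections do not strictly contradict each other, and silence alone would not be a finding. But the article does name its covariates, and the list does not follow from its own reason for collecting the index. The placement under Secondary outcomes is wrong whatever the analysis plan says.

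2. **The evidence of prognostic value is thin.** A reader might infer that comorbidity is a known prognostic factor and that precision is definitely lost. The article says only that other diseases might matter, and it quantifies nothing. It also speaks of physical outcomes. QUALEFFO has a physical function domain, but that is not a statement that comorbidity predicts its score. This stands, and it limits the point to Timed Loaded Standing and the physical tests.

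3. **Chance imbalance is not a defect.** A reader might infer that leaving it in distorts the treatment estimate. Under randomisation it is random error that the interval and test already cover, with no bias and no type I error inflation. This stands in full.

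4. **The index may serve only to describe the sample.** Baseline assessment does introduce Table 1 as summarising the baseline measures. That is a legitimate use, but it does not explain the secondary-outcome label.

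**Conclusion.** This is a minor point. The index is a pre-randomisation variable filed among outcomes, and a modest possible gain in precision is left unused for the physical outcomes, including a primary one. Over an assumed partial correlation of 0.1 to 0.3, the standard error would fall by about 0.5% to 4.6%, equivalent to about 2 to 20 participants per arm of 200. The true partial correlation, and so the gain, will be nearer the lower end or below it if age, or the baseline outcome if it is also in the model, carries part of the same information.

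A reader might also infer that the trial is underpowered without this adjustment. The documents do not support that: the stated power reproduces without it, and in the simulation adjustment adds at most 96.8 − 95.9 = 0.9 percentage points over the assumed range. No conclusion of the trial is shown to depend on the choice.

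**What to change.** - In Secondary outcomes and Table 1, describe the index as a baseline covariate and remove it from the outcomes.
- In Statistical analysis, add the baseline index to prior fracture history and age, at least for Timed Loaded Standing and the physical secondary outcomes. If it is deliberately left out, say why.
- Make the change before unblinding, so that it cannot be read as a covariate chosen after seeing results.

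The cost is a few words, one model parameter out of up to 600 participants, and a stated way of handling an occasional missing baseline score. No new data are needed.

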### Objectives

This paper describes the trial protocol for a large, pragmatic RCT to assess the effects of a physiotherapy intervention based on exercise or manual therapy compared to usual care for people with osteoporosis and a clinically diagnosed vertebral fracture.

The secondary objectives are: 1) to compare the effects of manual therapy with exercise therapy; 2) to investigate the acceptability and adherence to the physiotherapy programmes for both patients and therapists; 3) to conduct a parallel health economic analysis to assess the cost effectiveness of the different treatment strategies from an NHS, Social Services and patients’ perspective; and 4) to conduct a nested qualitative study to explore the experiences and views of people with osteoporosis and vertebral fracture regarding their treatment, their perceptions regarding the appropriateness and acceptability of the interventions and to explore the factors influencing their adherence to the intervention programmes.

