## Methods/Design

### Trial design

The trial will be a prospective, multi-centre assessor-blinded, three-arm RCT with a nested qualitative study and an adaptive design. Patients will be randomised between three arms: usual care (control) group (A), manual therapy (B) and exercise therapy (C). Those in the usual care arm will receive a single session of education and advice, and those in the active treatment arms (B + C) will be offered up to seven individual physiotherapy sessions over 12 weeks. Clinical assessment will be performed at baseline (week 0), 4 months and 12 months, with postal questionnaires about QoL administered at 6 and 9 months. An interim analysis will be conducted once 75 participants are recruited to each arm and have completed their 4 month follow-up. Following this interim analysis the study may be adapted. If both intervention arms are sufficiently promising and sufficiently similar the study will not be adapted and recruitment will continue into both intervention arms. If one arm, manual therapy or exercise therapy, is not sufficiently promising relative to control or sufficiently similar to the other intervention arm, this arm will be dropped from the study and the study will be adapted to continue as a two arm RCT with participants randomised between the control and remaining intervention arm. If neither arm is sufficiently superior to the usual care arm the trial will be stopped.

The protocol conforms to CONSORT guidelines for non-pharmacological studies [29] (Figure 1).

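### If an arm is dropped at the interim, the final analysis contains no 12-month manual-versus-exercise comparison, although that comparison is an unconditional secondary objective

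*Protocol article*

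**What the plan says.** The Objectives section of the protocol article lists, as the first secondary objective, "to compare the effects of manual therapy with exercise therapy". No condition is attached.

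The Trial design section allows both arms to go on: "If both intervention arms are sufficiently promising and sufficiently similar the study will not be adapted and recruitment will continue into both intervention arms". Otherwise the weaker arm is closed and the trial continues with two arms, or the trial stops.

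The Interim analysis decision rules section gives two guideline rules, both on mean QUALEFFO change at 16 weeks:
- Rule (a) compares each intervention with control. If its mean change "is not more than 0.5 points greater than that for the control arm, that intervention arm will be dropped from the study".
- Rule (b) compares the interventions with each other. If one group's mean change "is more than 2 points higher than for the other group", the lower one is dropped.

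The Statistical analysis section then fixes who is analysed: "The final statistical analysis will include data from patients from the control arm and intervention arm(s) continuing beyond the interim analysis", using data from both stages. For multiplicity it describes "applying a Dunnett correction to the comparisons between the intervention arms and the control arm at the first stage and at the second stage", with an exception when an arm is dropped. The Health economics analysis section likewise covers only control and the selected intervention(s).

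**The concern.** The objective and the analysis population do not fit together. Manual versus exercise is promised whatever the interim shows, but the final analysis can deliver it only if both arms continue. Rule (b) closes an arm because the two interventions look different, so the 12-month comparison is most likely to be missing when there is a real difference to estimate. The Background section says it is unknown whether exercise is more effective than manual therapy and that longer-term outcomes need study. The primary outcomes are at 1 year. What is at stake is a stated secondary objective and the use of 12-month data from people already randomised to the closed arm. The confirmatory comparison with control is not at risk.

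**Working it through.** **1. Inputs (Sample size and Interim analysis decision rules sections).** There are 75 per arm at the interim ("The sample size for the interim analysis was chosen to be 75 per arm"). The standard error of an interim difference is 0.82 points, the thresholds are 0.5 and 2 points, and the design effect is 0.4 SD.

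Implied SD: 0.82 / √(2/75) = 0.82 / 0.1633 = 5.02 points. An effect of 0.4 SD is then 0.4 × 5.02 = 2.0 points.

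**2. Reproducing the plan's own figures.**
- Probability of dropping an arm equal to control under rule (a): Φ(0.5 / 0.82) = Φ(0.61) = 72.9%. The article says about 73%.
- Probability of stopping the trial when neither arm works (bivariate normal, correlation 0.5 from the shared control): 59.3%. The article says about 60%.
- Power at effects 0.4 and 0, by simulating both rules followed by a closed Dunnett test with inverse-normal combination: 94.2%. This assumes one-sided 0.025, 125 per arm in stage 2, and perfect correlation between 16-week and 12-month arm means. The article says 94%.

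The rules as read here match the rules the article used.

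**3. How often the 12-month head-to-head is lost.** Three independent arm means were simulated, each with standard error 5.02 / √75 = 0.58, and rules (a) and (b) were applied:

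| True effects (SD) | Both continue | Exactly one dropped | Both dropped |
|---|---|---|---|
| 0.4 and 0 | 20% | 77% | 3% |
| 0.4 and 0.2 | 68% | 30% | 2% |
| 0 and 0 | 13.5% | 27% | 59% |
| 0.4 and 0.4 | 93% | 6% | 1% |

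The final analysis as written supports manual versus exercise only in the first results column.

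**4. What could be estimated after a drop.** The standard error in SD units is √(2/n) with n per arm. Power at 0.4 SD, two-sided 0.05, is Φ(0.4/SE − 1.96).
- n = 75: SE = √(2/75) = 0.163, and power = Φ(2.449 − 1.96) = Φ(0.49) = 69%.
- n = 200 (no drop): SE = 0.100, and power = Φ(4.00 − 1.96) = 98%.

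More than 75 per arm will be enrolled when the decision is taken, because recruitment runs on while the 75th participant reaches 4 months. The article gives no accrual curve. As an assumption, take uniform recruitment of 600 over 20 to 22 months (first randomisation in September or November 2013, last 12-month visit in June 2016) and 0 to 3 months to decide:
- Low end: 600/22 = 27.3 per month. 225 are reached at 8.2 months, and 4 months later about 334 are randomised (111 per arm). SE = √(2/111) = 0.134, power 85%.
- High end: 600/20 = 30 per month. 225 are reached at 7.5 months, and 7 months later 435 are randomised (145 per arm). SE = √(2/145) = 0.117, power 93%.

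Slow site opening would change these numbers, so 75 per arm is the safe basis. All figures are before attrition.

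**5. Does leaving out the dropped arm damage the test against control?** The same simulation at effects 0 and 0 gives familywise error 0.0224 when the stage-1 Dunnett p-value uses both arms, and 0.0228 when it uses only the retained arm's statistic. Both are below 0.025. Power at 0.4 and 0 is 94.2% either way. With no stage-1 correction at all after a drop, the error would be 0.028.

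**The case against.** The strongest reply is that this is how a selection design works. The article says openly that the trial may become a two-arm trial, and giving up the full head-to-head comparison is the price. If both arms continue, both are analysed. Rule (b) compares the two interventions directly at the interim in every case. The 77% figure belongs to one scenario, and with two equally effective arms the loss occurs in only 6% of trials.

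Much of this stands. The objective is lost conditionally, not always, and the frequency must be shown as a range. The design may properly give up a confirmatory claim about a dropped arm. But rule (b) is a monitoring guideline on one outcome at 16 weeks and does not replace a 12-month estimate. Nor does selection require that no estimate be made, and the objective is not worded as conditional.

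A reader might infer two stronger points, and the article supports neither.
- **That the stage-1 Dunnett test lacks its data.** The Statistical analysis section names the intervention arms, in the plural, at the first stage. The proviso in "at the first stage and at the second stage unless an intervention arm is dropped" reads most naturally as limiting only the second-stage correction. Even a Dunnett p-value from the retained arm alone keeps the error below 0.025.
- **That falls and fractures in a closed arm go unreported.** The Secondary outcomes section collects these events monthly over the year with no exception by arm, and the article commits to CONSORT reporting.

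Whether participants in a closed arm are followed to 12 months is not stated. The article condenses a fuller protocol, so that silence is not counted against it.

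**Conclusion.** The point holds in a limited form. The analysis population in the Statistical analysis section and the unconditional first secondary objective cannot both stand once an arm is dropped. Exactly one arm is dropped in about 6% to 77% of trials over the four scenarios examined, and the top of that range is the case where one therapy has the design effect and the other has none. These probabilities rest on normal arm means, the SD of 5.02 implied by the stated standard error, and the guideline rules being followed without override by the monitoring or steering committee.

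A useful though imprecise estimate is available after a drop: standard error about 0.16 SD with 75 per arm, and smaller if more are randomised before the decision. Type I error control and the stated 94% power for the comparison with control are not called into question by this point. The change is worth making because it restores a stated objective from participants already counted in the 600.

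**What to change.** Keep the sentence on continuing arms for the confirmatory comparison with control, and add wording to this effect: *All randomised participants, including those in an arm closed at the interim, are analysed as randomised in secondary analyses. Manual versus exercise therapy at 12 months is estimated with a 95% confidence interval from participants randomised while both arms were open, and is reported with a note that one arm was closed on interim results.*

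As an optional clarification, add that a dropped arm's stage-1 data enter the stage-1 Dunnett test. If the trial team prefers not to make the 12-month comparison after a drop, the minimum is to make the first secondary objective explicitly conditional on both arms continuing.

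The cost is wording, modest analysis work, and any 12-month visits for already enrolled participants that are not already planned. The resulting estimate has limited precision and carries some selection bias, because the arm was closed on early results from some of the same participants. It should be presented as estimation, not as a confirmatory test.
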